**Secondary Endpoint 3:**
Variation in FSH, estradiol, and AMH levels at 4 hours post-injection, defined as the difference between concentrations measured at H8 (4 hours after injection) and H0 (4 hours before injection).

# METHODOLOGY

### ****5.1 Study Design****

This is a **single-center, phase I pilot study** with **two parallel groups**.

The study will be proposed during endocrinological gynecology consultations to all patients meeting the inclusion criteria. After obtaining written informed consent, participants will be assigned to one of the two dose groups.

During the 4 hours preceding Ganirelix injection*, baseline LH secretion and pulsatility, as well as baseline levels of androgens, FSH, estradiol, and AMH, will be measured.

Subsequently, patients will receive a **low-dose injection of Ganirelix***. LH secretion and pulsatility will be monitored for **4 hours following the injection**, along with measurements of androgens, FSH, estradiol, and AMH at **H8**.

The expected outcome is to identify the Ganirelix* dose that reduces the abnormal frequency of LH pulses in women with PCOS to values comparable to normal conditions (approximately a 30% reduction).

As **secondary outcomes**, reproductive markers (serum levels of testosterone, androstenedione, LH, FSH, estradiol, and AMH) as well as glucose, insulin, and liver function parameters will be assessed before and after the 4-hour GnRH antagonist treatment period.

### ****5.2 Measures Taken to Minimize Bias****

Each participant will serve as her own control in this study, thereby minimizing potential bias.

The phenotypic diversity among women with PCOS — particularly regarding lean versus obese status — has a significant impact on mean plasma LH levels. To reduce variability, this pilot study will focus exclusively on **lean women with a highly uniform PCOS phenotype**, defined as follows:

- Age between **18 and 35 years**,
- **BMI below 30 kg/m²**,
- **Hyperandrogenism** (total testosterone > 0.39 ng/mL),
- **Elevated plasma LH** (> 8 IU/mL),
- **Elevated plasma AMH** (> 28 pmol/L).

#### ****5.2.1 Randomization****

No formal randomization will be performed, as it is not considered relevant given the small sample size required.

The **first 10 patients** will receive a Ganirelix dose of 0.025 mg*, and the **next 10 patients** will receive a Ganirelix dose of 0.0625 mg*.

#### ****5.2.2 Blinding****

Neither the participants nor the laboratory personnel performing the hormonal assays will be aware of the dose administered.

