# STUDY OBJECTIVES

### ****3.1 Primary Objective****

To assess the effect of Ganirelix on the reduction of luteinizing hormone (LH) pulse frequency, comparing two different dose levels.

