# EVALUATION CRITERIA

### ****4.1 Endpoint for the Primary Objective****

The expected decrease in LH pulse frequency before and after Ganirelix* administration is estimated to be between 20% and 30%.
To be considered an LH pulse or peak, the value had to show an increase of more than 20% compared with one of the two preceding points, followed by a decrease of more than 10% in one of the two subsequent points.

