### ****7.2 Study Procedures****

This is a **phase 1 pilot study** with **two parallel groups**, evaluating the efficacy of two different doses of Ganirelix in **20 women with PCOS**, defined by **oligo-/anovulation**, **hyperandrogenism**, and **elevated circulating LH levels**.

An **intravenous cannula** will be inserted, and **blood samples will be collected every 10 minutes** for a **4-hour baseline period** starting at 8:00 a.m.
Subsequently, Ganirelix will be administered as a **single subcutaneous injection** at one of two doses:

- **0.025 mg** (n = 10 PCOS patients)
- **0.0625 mg** (n = 10 PCOS patients)

These doses correspond to approximately **one-tenth and one-quarter** of the standard clinical dose used in **IVF protocols** to achieve full LH suppression.

Following Ganirelix administration, blood sampling will continue every 10 minutes for an additional **4-hour period**.

The **primary endpoints** include mean LH levels, as well as LH pulse **frequency and amplitude**, evaluated before and during treatment with Ganirelix.
In healthy women, LH surges occur approximately every 90 minutes during the early follicular phase, whereas **lean women with PCOS** may exhibit **one or more LH pulses per hour**.

The expected outcome is to determine the Ganirelix dose that reduces the **abnormally elevated frequency** of LH pulses by approximately **20–30%**, bringing them closer to normal physiological values.

**Secondary outcomes** include reproductive hormone markers — **serum testosterone, androstenedione, LH, FSH, estradiol, and AMH levels** — measured before treatment and **4 hours post-injection**.

The **pretreatment period** (baseline LH secretion and pulsatility) will be compared to the **4-hour post-antagonist period.**An **LH pulse** will be defined as a **≥20% incremental change** in LH concentration between the nadir and the subsequent peak, as previously described in similar clinical studies (Ref. 25).

The degree of gonadotropin suppression will be calculated as a **percentage of inhibition** relative to the pre-antagonist period:

$$\text{Inhibition (\%)}=\frac{(\text{PRE mean}-\text{nadir})}{\text{PRE mean}}\times100$$

as described previously (Ref. 26).
Hormone nadir levels will be computed using a **moving average**.
For LH, a **6-point moving average** (equivalent to 1 hour of sampling) will be used, as the nadir is expected to occur within the 10-minute sampling intervals.

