### ****8.2 Labelling of the Investigational Medicinal Product****

The investigational product will be **labelled in accordance with Good Clinical Practice (GCP) and applicable regulatory requirements**, clearly identifying:

- The **name of the investigational product (Ganirelix)**
- The **dose and concentration after dilution**
- The **study identification code**
- The **participant identification number**
- The **administration route (subcutaneous)**
- The **storage conditions**
- The **mention “For clinical trial use only – Not for sale”**

Labelling and documentation will be managed by the **hospital pharmacy** under the supervision of the **principal investigator**.

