**Description of Data**
Baseline demographic and clinical characteristics will be described by treatment group.
Quantitative variables will be summarized as mean (standard deviation or standard error). The normality of data distributions will be evaluated using the Shapiro–Wilk test.

For normally-distributed data, data will be compared using unpaired two-sided Student’s *t*-test. For non-normally distributed values, Mann-Whitney U test will be used.

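### The blind in 5.2.2 covers dose only, for participants and assay staff: it leaves the pulse count behind the before/after contrast unprotected, and it conflicts with the label required in 8.2

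*Protocol*

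**What the plan says.** **Masking.** Section 5.2.2 reads in full: "Neither the participants nor the laboratory personnel performing the hormonal assays will be aware of the dose administered". Two groups are masked, and only to dose. The investigator, the nurse who dilutes the product (8.1), the person who counts pulses and the statistician are not mentioned. Nor is masking to period, that is, to whether a sample was drawn before or after injection.

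**Contrast.** Section 4.1 frames the primary endpoint within the woman: "The expected decrease in LH pulse frequency before and after Ganirelix* administration is estimated to be between 20% and 30" per cent. Section 7.2 says LH level, pulse frequency and amplitude are "evaluated before and during treatment with Ganirelix". Section 5.2 offers own-control comparison as the protection against bias. There is no placebo arm. The documents also point to a second contrast: the primary objective in 3.1 speaks of "comparing two different dose levels", and the only comparison tests named are unpaired ("For normally-distributed data, data will be compared using unpaired two-sided Student’s" t-test, or Mann-Whitney).

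**Counting.** Section 4.1 asks for a rise of over 20% relative to either of the two samples before, "followed by a decrease of more than 10% in one of the two subsequent points". Section 7.2 asks for a rise of at least 20% from trough to next peak and sets no condition on the fall. The primary endpoint analysis refers back to a method in 1.1.2.

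**Label and allocation.** Section 8.2 lists "dose and concentration after dilution" among the label contents, together with the participant number. Section 5.2.1 gives one dose to the first ten women and the other to the next ten.

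**The concern.** The assay produces concentrations. The primary endpoint comes into being one step later, when a series of samples is turned into a number of pulses. Section 5.2.2 is silent on that step. The contrast that carries the efficacy answer is one in which the dose is constant within each woman, so hiding the dose does nothing for it. If someone who can see the injection time decides which peaks count, in a protocol that announces both the direction and the size of the expected change, the design contains nothing to keep that knowledge out of the count.

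The second part is an inconsistency on the page. The participant is not to know her dose, yet the product injected into her while she is awake must be labelled with it. The between-dose comparison in 3.1 is the one the dose blind is meant to serve, so this matters for that contrast.

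**Working it through.** The protocol states that no power calculation was made, so there is no planned figure to reproduce. The check has three parts.

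**1. Does the blind match the contrast?**

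- Before versus after (4.1, 5.2, 7.2): protecting it needs masking to period. None is provided for anyone.
- Between doses (3.1 and the named tests): protecting it needs masking to dose. It is provided for participants and assay staff, and not for a separate pulse reader.

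**2. How much is one pulse worth?** Section 7.2 puts lean women with PCOS at one pulse per hour or more, and healthy women at about one per 90 minutes.

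- Pulses per window = 240 min / interval.
- At 60 min: 240/60 = 4. The target is 0.20 × 4 = 0.8 to 0.30 × 4 = 1.2 pulses. One pulse is 1/4 = 25%.
- At 50 min (an assumption, for a faster rate): 240/50 = 4.8. The target is 0.96 to 1.44 pulses. One pulse is 1/4.8 = 21%.
- If one peak were called differently in every second woman at four pulses per window: 0.5/4 = 12.5%.

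The whole target effect is therefore about one pulse per woman per window.

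**3. Does the counting step leave room for choice?** The rules in 4.1 and 7.2 differ in the reference point for the rise and in whether a fall is needed. The 4.1 rule can also be read with or without requiring the value to be a local peak. To see whether this matters, both rules were applied to the same simulated 25-sample windows (240/10 + 1 = 25), 3,000 per setting. The assumptions, none of them from the protocol, were a baseline of 8, each pulse adding 50% of baseline, a 60-minute half-life, pulse spacing varying by 15% of the interval, and assay CV of 3%, 5% or 8%.

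| Interval | CV | Mean count, 4.1 (local peak) | Mean count, 4.1 (literal) | Mean count, 7.2 | Windows where 4.1 (local peak) and 7.2 differ |
|---|---|---|---|---|---|
| 60 min | 3% | 2.10 | 3.08 | 3.75 | 89% |
| 60 min | 5% | 2.35 | 3.26 | 3.61 | 79% |
| 60 min | 8% | 2.72 | 3.67 | 3.83 | 73% |
| 90 min | 3% | 1.16 | 1.77 | 2.65 | 88% |
| 90 min | 5% | 1.53 | 2.22 | 2.65 | 76% |
| 90 min | 8% | 2.13 | 2.91 | 3.10 | 67% |

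Under these assumptions, the choice of rule changes the count in 67–89% of identical windows. The simulation says nothing about which way a reader would lean.

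**Label and allocation, side by side.** Section 5.2.2 says the participant will not know her dose; 8.2 prints it on the product prepared for her. Under 5.2.1, anyone who knows her place in the enrolment order and the allocation rule knows the dose without seeing a label. Annexe 3 has samples reaching the laboratory as women are enrolled, so their order is visible there too.

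**The case against.** **The rules are arithmetic.** Both definitions are thresholds on assay values. One rule, fixed in advance and run by program on both windows, would leave almost no room for a reader's expectations. This is right, and it is the simplest remedy. It does not dispose of the point, because the protocol does not fix one rule and does not say that a program applies it.

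**Silence is not evidence.** A reader might infer that the person counting pulses knows both dose and period. The protocol does not say so: it names no pulse reader. If assay staff count, 5.2.2 masks them to dose. The analyses are described as done independently by a biostatistics department, and a statistical analysis plan or laboratory manual not shown here may assign the task. The supportable statement is that 5.2.2 provides no such masking. That remains a protocol matter, because 5.2.2 sets out who is masked and stops short of the step that creates the endpoint.

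**The 25% is not a bias estimate.** One might read it as the error to expect. It would arise only if a peak were dropped after injection in every woman and never before. Nothing in the documents supports that.

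**Before/after is not the only primary contrast.** Section 3.1 and the unpaired tests point to a dose comparison, for which the existing blind is relevant. This stands.

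**The label may never be read.** It is a product label. It is not shown to be on the blood tubes, so the inference that it unmasks the assay laboratory is unsupported. Even for the participant, the blind fails only if she sees it. What stands is that the plan requires the dose on the label and provides nothing to keep it from her. Enrolment-order allocation is the larger threat to the dose blind.

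**Coded segments are an imperfect mask.** Falling LH may reveal the later segment, and a strict cut at injection removes neighbouring samples that the 4.1 rule needs. Both are true, and the fix allows for them.

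**Conclusion.** The point holds in a limited form. The stated blind does not cover the before/after contrast on which 4.1 and 7.2 rest the efficacy answer, and it makes no provision for whoever derives the pulse counts. Two differing rules and an untraceable cross-reference leave choices open at that step. The endpoint is sensitive to such choices: one pulse is about 25% at four pulses per window and about 21% at an assumed 4.8, roughly the size of the whole target. No direction or amount of bias has been shown. The simulated disagreement between rules depends on assumed pulse shape and assay error.

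Sections 5.2.2 and 8.2 need reconciling as they stand. This would remain so if allocation were changed.

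For a 20-woman exploratory pilot this does not undo the study. The protection is cheap, and the study is meant to supply estimates for a confirmatory trial, so the change is worth making before any pulses are counted.

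**What to change.** **Section 5.2.2.** State who or what derives the pulse counts, and choose one of two routes:

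- *Preferred:* one pre-specified pulse rule, applied by script to every series. Align 4.1 and 7.2 with that rule and correct the reference to 1.1.2.
- *Otherwise:* a reader who receives coded series without dose, clock time or period label. That makes 20 women × 2 periods = 40 segments.

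In either case, keep two flanking samples on each side of the injection so that peaks near the boundary can be evaluated, and say to which window the T240 sample belongs so that a peak there is not counted twice. Lock the counts before unmasking. List who is not masked, such as the nurse who prepares the product.

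**Section 8.2.** Put a treatment code on the label seen at the bedside and hold the dose in the pharmacy and preparation record. The code closes only this route: while dose follows enrolment order, rank still reveals it, and 5.2.2 should acknowledge that.

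**Cost.** A script or recoding step, a few sentences and a revised label, with no extra samples or staff and a short delay before counts can be viewed by period. Masking a human reader to period will be incomplete, because suppressed LH may give the later segment away and the overlapping flanking samples could let two segments be matched. Both are reasons to prefer the script.

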### ****5.3 Number of Subjects Required****

A total of **20 patients** will be included, with **10 patients per treatment arm**.

For details regarding the calculation of the required sample size, refer to **Section 11.1 – Calculation of the Number of Subjects Required.**

##

## ****6 ELIGIBILITY CRITERIA AND FOLLOW-UP PROCEDURES****

### ****6.1 Inclusion Criteria****

- Female participant
- Age between **18 and 35 years**
- **Minimum body weight:** 51 kg
- **Body Mass Index (BMI):** below 30 kg/m²
- **Diagnosis of PCOS**, defined by **AMH > 28 pmol/L**, **LH > 8 IU/mL**, and **total testosterone > 0.39 ng/mL**
- No use of **hormonal contraception** or **hormonal treatment** within the past **2 months**
- **Written informed consent** obtained for participation in this **Category 1 clinical trial**
- **Covered by national health insurance**
- Willing and able to comply with all **study procedures** and **study duration**

### ****6.2 Exclusion Criteria****

- Ongoing treatment with **medications affecting metabolism**, such as **metformin**
- **Pregnant woman**
- **Inability to understand** the information sheet
- **Hypersensitivity** to the active substance Ganirelix, to any **structural analogues of gonadotropin-releasing hormone (GnRH)**, to **exogenous peptide hormones**, or to any **excipients**
- **Administrative reasons**, including:
  - Inability to receive adequate informed information
  - Inability to participate in the entire study
  - Lack of **social security coverage**
  - **Refusal to sign** the informed consent form

### ****6.3 Criteria for Study Withdrawal and Early Termination****

- Occurrence of **discomfort** during the 8-hour study period
- **Severe allergic reaction** requiring medical and/or pharmacological intervention
- **Withdrawal requested by the participant**

### ****6.4 Prohibition of Simultaneous Participation and Exclusion Period****

#### ****6.4.1 Simultaneous Participation in Another Study****

No. Participants may not be enrolled in any other clinical trial simultaneously.

#### ****6.4.2 Post-Study Exclusion Period****

None.

#### ****6.4.3 Registration in the Volunteer Database (VRB File)****

Not applicable.

## ****7 CONDUCT OF THE STUDY****

### ****7.1 Feasibility and Experience of the Investigative Team****

The investigators involved in this study are physicians with extensive clinical and research experience in **polycystic ovary syndrome (PCOS)**.
Ganirelix is a compound routinely used by the medical team in **reproductive medicine**.

A **state-registered nurse** and suitable **clinical facilities** are available to conduct all study-related procedures.

### ****7.2 Study Procedures****

This is a **phase 1 pilot study** with **two parallel groups**, evaluating the efficacy of two different doses of Ganirelix in **20 women with PCOS**, defined by **oligo-/anovulation**, **hyperandrogenism**, and **elevated circulating LH levels**.

An **intravenous cannula** will be inserted, and **blood samples will be collected every 10 minutes** for a **4-hour baseline period** starting at 8:00 a.m.
Subsequently, Ganirelix will be administered as a **single subcutaneous injection** at one of two doses:

- **0.025 mg** (n = 10 PCOS patients)
- **0.0625 mg** (n = 10 PCOS patients)

These doses correspond to approximately **one-tenth and one-quarter** of the standard clinical dose used in **IVF protocols** to achieve full LH suppression.

Following Ganirelix administration, blood sampling will continue every 10 minutes for an additional **4-hour period**.

The **primary endpoints** include mean LH levels, as well as LH pulse **frequency and amplitude**, evaluated before and during treatment with Ganirelix.
In healthy women, LH surges occur approximately every 90 minutes during the early follicular phase, whereas **lean women with PCOS** may exhibit **one or more LH pulses per hour**.

The expected outcome is to determine the Ganirelix dose that reduces the **abnormally elevated frequency** of LH pulses by approximately **20–30%**, bringing them closer to normal physiological values.

**Secondary outcomes** include reproductive hormone markers — **serum testosterone, androstenedione, LH, FSH, estradiol, and AMH levels** — measured before treatment and **4 hours post-injection**.

The **pretreatment period** (baseline LH secretion and pulsatility) will be compared to the **4-hour post-antagonist period.**An **LH pulse** will be defined as a **≥20% incremental change** in LH concentration between the nadir and the subsequent peak, as previously described in similar clinical studies (Ref. 25).

The degree of gonadotropin suppression will be calculated as a **percentage of inhibition** relative to the pre-antagonist period:

$$\text{Inhibition (\%)}=\frac{(\text{PRE mean}-\text{nadir})}{\text{PRE mean}}\times100$$

as described previously (Ref. 26).
Hormone nadir levels will be computed using a **moving average**.
For LH, a **6-point moving average** (equivalent to 1 hour of sampling) will be used, as the nadir is expected to occur within the 10-minute sampling intervals.

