| **Intervention description** | An intra-venous cannula will be inserted and blood will be sampled at 10-min intervals for a 4-h baseline period commencing at 0800 h. Ganirelix will be then administered subcutaneously at single-dose regimen at 0.0625 mg (n = 10 women with PCOS). After Ganirelix administration sampling will continue at 10-min intervals for 4 h. |
| **Name of arm 2** | Pilot phase-0, parallel, clinical study.  Test the efficacy of Ganirelix administered subcutaneously at single-dose regimen of 0.025 mg in 10 women with PCOS, in rectifying LH pulse frequency and LH amplitude. |
| **Intervention (at least one intervention)** | Drug (including placebo)  Radiation  Other  Device (including sham) Behavioral  Biological / vaccine  Genetic  Procedure / surgery  Dietary supplement |
| **Intervention name** | Ganirelix (Orgalutran) |
| **Intervention description** | An intra-venous cannula will be inserted and blood will be sampled at 10-min intervals for a 4-h baseline period commencing at 0800 h. Ganirelix will be then administered subcutaneously at single-dose regimen at 0.025 mg (n = 10 women with PCOS). After Ganirelix administration sampling will continue at 10-min intervals for 4 h. |
|  | **Primary Outcome measure** |
| **Title** | Serum LH level every 10 minutes for 8 hours |
| **Time point at which primary outcome measure is assessed** | The degree of gonadotropin suppression will be determined by calculating the percent inhibition from the pre-antagonist period [(mean PRE - nadir)/mean PRE] x 100, where nadir hormone levels will be calculated using a moving average. |
|  | **Secondary outcome measures, repeating as many times as 2nd outcomes** *Noter les 5 principaux critères d’évaluation* |
| **Title** | Measurement of serum testosterone and androstenedione, FSH, estradiol and AMH levels |
| **Time point(s) at which Secondary outcome measure is assessed** | Serum testosterone and androstenedione, FSH, AMH and estradiol levels at the beginning and at the end of the 8 hours |
| **Inclusion criteria** | -women aged 18 to 35  -women with PCOS with AMH> 28 pmol / L, LH> 8 IU / mL and testosteronemia > 0.39 ng/mL  - no hormonal treatment or contraception for 2 months  - women covered by the Social Security system  Non obese women |
| **Exclusion criteria** | -hormonal treatment or hormonal contraception  - Metformin treatment  -pregnant woman  -inability to understand the newsletter |

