### ****4.2 Endpoints for the Secondary Objectives****

**Secondary Endpoint 1:**
The variation in LH secretion before and after Ganirelix injection will be calculated as the mean LH (the average of all LH values over the study period) and basal LH, corresponding to the mean of the five lowest LH values over the study period. The total LH corresponds to the sum of all LH values at T0-T240 and T240-T480.

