# STATISTICAL ANALYSES

**General Principles**
All statistical analyses will be performed independently by the Department of Biostatistics, University of Lille, under the supervision of [name]. Analyses will be conducted using 10.0.2 GraphPad Prism software (GraphPad; San Diego, CA, USA).

All analyses will be performed on the per-protocol population, unless otherwise specified. The level of statistical significance will be set at α = 0.05 (two-sided). No adjustment for multiple testing will be applied, and all secondary analyses will be considered exploratory. Results will be presented as effect size estimates with corresponding 95% confidence intervals (95% CI).

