**Primary Endpoint Analysis**
The primary endpoint is the reduction in LH pulse frequency during the 4-hour period following Ganirelix administration.
Analysis will include:
- Determination of LH pulse frequency using the method described above (1.1.2).

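### The primary endpoint is LH pulse frequency in most of the protocol, three LH measures in section 7.2, and percent inhibition to a nadir in the draft registration text

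*Protocol*

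**What the plan says.** **Pulse frequency alone.** The Primary Endpoint Analysis in the Statistical Analyses section states: "The primary endpoint is the reduction in LH pulse frequency during the 4-hour period following Ganirelix administration". The full study synopsis, section 3.1 (Primary Objective) and section 4.1 (Endpoint for the Primary Objective) agree with it.

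**Three measures.** Section 7.2 (Study Procedures) uses the plural and says that the primary endpoints "include mean LH levels, as well as LH pulse" frequency and amplitude, before and during treatment. The same section lists serum LH again among the secondary outcomes. Mean LH is also Secondary Endpoint 1 in the synopsis and in section 4.2: "The variation in LH secretion before and after Ganirelix injection will be calculated as the mean LH".

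**Percent inhibition.** The synopsis drafted for ClinicalTrials.gov registration titles the primary outcome "Serum LH level every 10 minutes for 8 hours" and defines it this way: "The degree of gonadotropin suppression will be determined by calculating the percent inhibition from the pre-antagonist period", with the nadir taken from a moving average. Pulse frequency does not appear in that primary-outcome entry. Section 7.2 gives the same formula, with a 6-point moving average for LH, but does not call it primary.

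**Error control.** General Principles sets a two-sided significance level of 0.05 and continues: "No adjustment for multiple testing will be applied, and all secondary analyses will be considered exploratory".

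**The concern.** A trial needs one identifiable primary result, fixed before anyone sees the data. Here a reader could report pulse frequency, mean LH, pulse amplitude or percent inhibition as primary and cite current protocol text for each.

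Two practical consequences follow. The outcome drafted for the registry is not the one that the statistics section says will be analysed. And section 13 asks monitors to verify the primary endpoint, which cannot be done unambiguously while three versions stand.

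The protocol also says that the results should support a later, adequately powered trial. That trial will inherit whichever measure is presented as primary here.

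**Working it through.** The plan gives no power or error-rate calculation for this point, so there is no figure to reproduce. The check is a comparison of the texts, followed by two illustrations.

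**1. The texts side by side**

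| Place in the protocol | What is labelled primary |
| --- | --- |
| Synopsis; 3.1; 4.1; Primary Endpoint Analysis | LH pulse frequency |
| 7.2 | Mean LH, LH pulse frequency, LH pulse amplitude |
| Registration synopsis | Serum LH, as percent inhibition from PRE mean to nadir |

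That is three versions and four distinct quantities. Mean LH is primary in one place and secondary in two others. No section gives an order of precedence.

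**2. Can the quantities disagree?**

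Section 7.2 expects one or more pulses per hour in lean women with PCOS, so a 4-hour window holds about 240/60 = 4 pulses. Suppose that 4 pulses also occur after injection, but smaller ones. The change in frequency is (4 − 4)/4 = 0%, while amplitude and mean LH both fall. One version shows no effect and the others show suppression.

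**3. Percent inhibition when the drug does nothing**

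Formula: (PRE mean − nadir)/PRE mean × 100. With 24 post-injection samples, a 6-point moving average gives 24 − 6 + 1 = 19 overlapping means, and the nadir is the smallest of them. With no drug effect their average is expected to lie near the PRE mean, so the smallest is expected to lie below it. The measure is therefore positive on average under no effect.

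A simulation gives a rough size. Its assumptions are a pulse interval of 50, 60 or 90 minutes, two pulse heights, a 60-minute half-life of LH, 5% assay CV and 4,000 runs per setting. Mean inhibition with no drug effect was 9.8% to 18.2%, and the value was positive in 82% to 91% of women. None of these LH-series assumptions comes from the protocol.

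**4. Error rate, for illustration only**

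Inputs: level 0.05, unadjusted (General Principles); three measures (7.2); 10 women per dose (5.3). Assumed: each measure is tested once, and the correlation between measures is as shown. The independent row is exact: 1 − 0.95³ = 14.3% and 1 − 0.95⁶ = 26.5%. The other rows come from 20,000 simulated sets of paired t-tests with n = 10. The last column assumes a separate set of tests in each dose group and is 1 − (1 − p)².

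| Correlation | Three tests, p | Same, in each of two doses |
| --- | --- | --- |
| Independent | 14.3% | 26.5% |
| 0.3 | 13.6% | 25.3% |
| 0.5 | 13.0% | 24.3% |
| 0.8 | 10.2% | 19.4% |
| 0.95 | 7.7% | 14.9% |

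All three measures come from the same LH series in the same women, so some correlation is likely. The protocol gives no value for it.

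**The case against.** The best defence is that this is a 20-woman exploratory pilot. The justification for having no power calculation says that the aim is preliminary data, not a formal hypothesis test. Results are to be given as estimates with 95% confidence intervals, and no success rule exists. All of that stands, and it rules out several stronger readings that a reader might infer:

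- **That a 5% family-wise rate is broken.** General Principles sets a significance level and openly declines adjustment. It never claims a family-wise rate.
- **That six tests are planned, with a 26% false-positive chance.** The Primary Endpoint Analysis names no test, and the only tests named in the section are unpaired two-group comparisons. Testing each dose separately is an assumption.
- **That success can be claimed on any version.** There is no success criterion to meet.
- **That the choice of dose depends on which version is primary.** Sections 5.1 and 7.2 both tie dose identification to pulse frequency alone.
- **That section 7.2 makes percent inhibition primary.** Only the registration synopsis does.
- **That the posted registry entry is wrong.** The protocol shows only a draft, and the actual record is not at hand.

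The defence does not remove the contradiction. The protocol still names a primary endpoint, still sets a significance level, and labels only the secondary analyses exploratory. The additional measures called primary in 7.2 therefore do not carry that label. A separate analysis plan might rank the measures, but sections 4.1 and 7.2 and the registration text would still disagree.

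**Conclusion.** The concern holds as an inconsistency in current text: three statements of the primary endpoint covering four quantities, with no rule of precedence. The result reported as primary could be chosen after the data are seen, and the drafted registry outcome differs from the analysed one. In this exploratory pilot the harm is selective labelling, not the loss of a confirmatory error rate.

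The size can only be illustrated. If the three measures in 7.2 were each tested once at 0.05, the chance of at least one false positive would be 14% under independence and about 8% to 14% at assumed correlations of 0.95 to 0.3. Separate testing by dose, which the protocol does not specify, would give about 15% to 26%. The upward tendency of percent inhibition follows from its definition; the figure of about 10% to 18% rests on an assumed LH series.

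**What to change.** Keep one primary endpoint throughout: the within-woman change in LH pulse count from T0-T240 to T240-T480, reported by dose. This is the version that most sections already carry.

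- **Section 7.2:** relabel mean LH and pulse amplitude as secondary, and state that percent inhibition is secondary.
- **Section 4.2 and the synopsis:** add pulse amplitude and percent inhibition to the secondary endpoints, which do not list them now.
- **Registration synopsis:** rewrite the primary outcome to match section 4.1 before registration, or amend the entry if it is already posted. Either way, do so before data are analysed.

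With a single primary endpoint no multiplicity procedure is needed. The cost is wording in these places, with no additional women, samples or assays. The sponsor should decide whether the change counts as substantial under Protocol Amendments in section 14.
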